#### Exclusion criteria

2.2.3

Cognitive dysfunction secondary to other conditions, such as central nervous system infections, head trauma, stroke, etc.Patients who have been taking medications that affect cognition within the past 3 months; or patients with a history of alcohol dependence or abuse of other psychoactive substances.Patients with severe visual acuity deficits, hearing impairment, severe aphasia, or other significant diagnoses.Severe internal diseases or central nervous system disorders, including but not limited to severe anemia.Patients with brain metastases, cerebral hemorrhage, cerebral thrombosis, traumatic brain injury, or severe cardiovascular disease.Patients who have undergone cognitive rehabilitation within the previous 3 months.Patients who are unable to independently complete the relevant scale due to other factors.

### Randomization and blinding

2.3

A computer-generated block randomization with 1:1 allocation will be used to assign 50 eligible participants. An independent statistician at the Beijing Hospital of Traditional Chinese Medicine, Capital Medical University will implement the randomization procedure using SPSS 25.0 statistical software (IBM Corporation, Armonk, NY, United States), employing randomly permuted blocks to ensure allocation concealment. The allocation information will become available only after the randomization procedure. Subsequently, a second individual will employ an opaque envelope containing a randomly sorted distribution card to assign patients to either the verum acupuncture group or the sham acupuncture group, based on their hospital visits. The research assistant responsible for randomization and acupuncturists are not blinded to the participant allocation. The data analysts and outcome assessors will not be aware of the allocated group.

To mitigate potential expectations regarding acupuncture treatment, patients will be informed that they will randomly receive one of two different acupuncture regimens. It is not possible to blind participants, owing to the different acupuncture points of the two groups. To minimize potential communication and interaction among participants, each patient will receive individualized acupuncture treatment and follow-up at separate times in distinct rooms. Due to the inherent nature of acupuncture intervention, blinding the acupuncturist is not feasible. Blinding will be applied to the outcome assessment. Data analysts and outcome evaluators will be blinded to the treatment allocation. Furthermore, to maintain the integrity of the study, communication between acupuncturists, participants, and outcome evaluators will be carefully structured to prevent any exchange of information. The assessor will be arranged to conduct assessment on different days from acupuncture treatment to avoid cross communication among the assessor, acupuncturists, and participants. The assessor will also be instructed not to acquire participants’ treatment information and their needling feelings. Prior to analysis, all data will be anonymized to ensure objectivity.

### Written informed consent

2.4

For any TNBC participants who meet the inclusion and exclusion criteria, they will be approached to participate in the study by one of the investigators from the study team. All participants will be provided with a written copy of the consent form detailing their random assignment to either verum acupuncture or sham acupuncture, as well as the potential benefits and risks. The investigator will be responsible for ensuring that the patient completely understands the potential risks and benefits of participating in the study and for answering any questions the patient may have. Responses will be in a language that the subject understands, with translation and visual aids as necessary. Participants can contact the investigator at any time to inform them of their decision and to ask any questions about the study through outpatient or inpatient visits, email contact, phone contact, WeChat contact or other web-based contacts. Prior to participating in the research, all participants will voluntarily sign the informed consent form. Withdrawal conditions: (1) Participants may choose to withdraw at any stage of the trial if they prefer not to receive the assigned treatment. (2) Participants must withdraw if adverse events (AEs) occur that require their withdrawal from the trial. (3) Participants are unable to complete protocol-specified procedures during the treatment or follow-up phases. (4) Participants can withdraw from the study for any reason. Participants will be asked if they agree to use their data for further analysis and sharing with researchers relevant to this study should they choose to withdraw from the trial.

### Interventions

2.5

The interventions for both the verum acupuncture group and the sham acupuncture group will be conducted in separate rooms within the outpatient clinic or on the ward. To mitigate treatment bias, two acupuncturists licensed by the Ministry of Health of the People’s Republic of China will administer acupuncture therapy. These practitioners are required to have more than 3 years of acupuncture experience. Prior to the commencement of the trial, the two acupuncturists will undergo professional training, encompassing the study objectives, treatment techniques, and quality assurance measures. Our adherence to the Standard Protocol Items: Recommendations for Interventional Trials (SPIRIT) 2013 statement ensures the incorporation of standardized protocol elements for clinical trials (34).

Participants will undergo acupuncture treatment twice weekly throughout the 8-week trial period, receiving either verum or sham acupuncture. The procedure will utilize sterile, disposable thin filiform needles (25–40 mm long and 0.25 mm in diameter; Hwatuo, Suzhou, China). Both treatment groups will receive 16 sessions over 4 weeks, with two sessions conducted per week. Each session, whether verum or sham acupuncture, will have a duration of approximately 20 min.

#### Verum acupuncture group

2.5.1

Participants in the verum acupuncture group will receive acupuncture treatment employing the approach of reconciling qi and blood and tonifying heart and mind. This method, derived from literature and expert acupuncture perspectives, involves inserting needles at specific acupuncture points. The acupoints for the verum acupuncture group are as follows:

Treatment will be administered to patients in the supine position at specific acupoints. These include the unilateral points CV17 (Danzhong), CV12 (Zhongwan), and CV6 (Qihai), as well as the bilateral points ST36 (Zusanli) and SP10 (Xuehai). The insertion angle for CV17 (Danzhong) is approximately 10° relative to the skin, with an optimal insertion depth of 12.5 mm. For CV12 (Zhongwan) and CV6 (Qihai), a 0.25 × 40 mm acupuncture needle is inserted to a depth of 25–40 mm. Similarly, ST36 (Zusanli) and SP10 (Xuehai) on both sides are treated with a 0.25 × 40 mm acupuncture needle, inserted to a depth of 20–25 mm.

Patients will receive treatment in prone positions at specific acupoints: GV20 (Baihui), GV16 (Fengfu), BL15 (Xinshu, bilaterally), BL45 (Yixi, bilaterally), HT5 (Tongli, bilaterally), and KI6 (Zhaohai, bilaterally). The insertion angle for GV20 (Baihui) is approximately 10–20° relative to the scalp, with an optimal insertion depth of 5 mm. GV16 (Fengfu) is inserted 12.5–25 mm deep, directed toward the lower jaw, using a 0.25 × 25 mm acupuncture needle. BL15 (Xinshu, bilaterally) and BL45 (Yixi, bilaterally) are inserted at a 10–20° angle relative to the skin, with depths of 7.5–12.5 mm and 12.5–20 mm, respectively, both utilizing 0.25 × 25 mm acupuncture needles. HT5 (Tongli, bilaterally) is inserted 7.5–12.5 mm deep, while KI6 (Zhaohai, bilaterally) is inserted 12.5–20 mm deep, both using 0.25 × 25 mm acupuncture needles. Comprehensive details of the acupoints for the verum acupuncture group are presented in Table 2.

**Table 2 tab2:** The details of verum acupoint localization.

Acupoint	Location
CV17 (Danzhong)	In the anterior thoracic region, at the same level as the fourth intercostal space, on the anterior median line.
CV12 (Zhongwan)	On the upper abdomen, 4 B-cun superior to the center of the umbilicus, on the anterior median line.
CV6 (Qihai)	On the lower abdomen, 1.5 B-cun inferior to the center of the umbilicus, on the anterior median line.
SP10 (Xuehai)	On the anteromedial aspect of the thigh, on the bulge of the vastus medialis muscle, 2 B-cun superior to the medial end of the basc of the patella (needled bilaterally)
ST36 (Zusanli)	On the anterior aspect of the leg, on the line connecting ST35 (Dubi) with ST41 (Jiexi), 3 B-cun inferior to ST35 (needled bilaterally)
GV20 (Baihui)	On the head, 5 B-cun superior to the anterior hairline, on the anterior median line.
GV16 (Fengfu)	In the posterior region of the neck, directly inferior to the external occipital protuberance, in the depression between the trapezius muscles.
BL15 (Xinshu)	In the upper back region, at the same level as the inferior border of the spinous process of the fifth thoracic vertebra (T5), 1.5 B-cun lateral to the posterior median line (needled bilaterally)
BL45 (Yixi)	In the upper back region, at the same level as the inferior border of the spinous process of the sixth thoracic vertebra (T6), 3 B-cun lateral to the posterior median line (needled bilaterally)
HT5 (Tongli)	On the anteromedial aspect of the forearm, radial to the flexor carpi ulnaris tendon, 1 B-cun proximal to the palmar wrist crease (needled bilaterally)
KI6 (Zhaohai)	On the medial aspect of the foot, 1 B-cun inferior to the prominence of the medial malleolus, in the depression inferior to the medial malleolus (needled bilaterally)

Prior to needle insertion, the designated areas will be thoroughly disinfected and acupuncture devices will be applied to each location. Subsequently, the acupuncturist will insert a disposable sterile needle into the acupuncture point, adhering to specific position and operation standards. The practitioner will perform appropriate insertion, lifting, and twisting techniques within the patient’s tolerance to elicit the “de qi” sensation, characterized by swelling, soreness, numbness, and heaviness. During the needle retention period, manual manipulation of the needles will occur every 10 min to maintain the “de qi” sensation. Each participant will undergo two 20-min treatment sessions per week, totaling 16 sessions over an 8-week period. Follow-up assessments will be conducted at weeks 8 and 16.

#### Sham acupuncture group

2.5.2

Patients in the sham acupuncture group will receive treatment at non-meridian and non-acupoint locations without eliciting the sensation of “de qi.” A superficial skin penetration technique will be employed. Several randomized controlled trials of acupuncture have utilized superficial skin penetration at non-acupoints without needle manipulation to avoid inducing the “de qi” sensation as a standard sham acupuncture method (35, 36). The non-meridian and non-acupoint groups will function as controls for the manual puncture and specific acupoint groups. Table 3 provides detailed information on the locations of non-acupoints. The acupuncture procedure and treatment frequency for the sham acupuncture groups will mirror those of the verum acupuncture groups.

**Table 3 tab3:** The details of sham acupoint localization (52, 53).

Non-acupoint (needled bilaterally)	Location
Non-acupoint 1	On the anteromedial aspect of the forearm, in the depression ulnar to the flexor carpi ulnaris tendon, the midpoint of the line connecting HT3 (Shaohai) with HT7 (Shaohai).
Non-acupoint 2	On the anteromedial aspect of the forearm, the junction of the upper one fourths and the lower three fourth of the line connecting HT3 (Shaohai) with HT7 (Shaohai).
Non-acupoint 3	On the lateral side of the lower leg, 3 B-cun above the tip of external malleolus, between Stomach Meridian of Foot-Yangming and Gallbladder Meridian of Foot-Shaoyang, at the same level as GB39 (Xuanzhong).
Non-acupoint 4	On the fibular aspect of the leg,3 B-cun inferior to the GB34 (Yanglingquan), On the fibular aspect of the leg,3 B-cun inferior to the GB34, between bladder Meridian of Foot-Taiyang and Gallbladder Meridian of Foot-Shaoyang.
Non-acupoint 5	On the radial side, the midpoint between the medial epicondyle of humerus and the styloid process of the ulna.
Non-acupoint 6	On the thigh,0.8 B-cun medial to the midpoint of the line linking the anterior superior iliac spine and the lateral end of the base of patella (needled bilaterally)
Non-acupoint 7	On the lateral side of the lower leg, 1 cun lateral to ST36 (Zusanli), between the Stomach Meridian of Foot-Yangming and the Gallbladder Meridian of Foot-Shaoyang.
Non-acupoint 8	On the middle of the abdomen, 1 B-cun lateral to ST25 (Tianshu), the midpoint between ST25 and SP15 (Daheng).
Non-acupoint 9	On the middle of the abdomen, 1.2 B-cun lateral to CV12 (Zhongwan).
Non-acupoint 10	On the medial anterior border of the upper arm, the junction of the deltoid and the biceps brachii.
Non-acupoint 11	At the lower border of the medial condyle of the tibia, 1 B-cun anterior and superior to LR7 (Xiguan) of the liver meridian.

### Sample size calculation

2.6

The sample size calculation was performed using PASS 15.0.5 software (NCSS, LLC). The estimation was based on the change in the 8-week Montreal Cognitive Assessment (MoCA) score post-treatment. Previous studies (17, 18) reported a total effective rate of 13.72% for the 8-week MoCA score in the sham acupuncture group after treatment. We anticipated a total effective rate of 58.33% for the 8-week MoCA score post-treatment in the verum acupuncture group. With a significance level of *α* = 0.05 (two-sided) and a power of 0.9, accounting for a 20% attrition rate, and an equal 1:1 group allocation, a minimum of 25 cases per group were determined necessary. Consequently, this study requires a total of 50 participants.

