## Statistical analysis

4

The statistical analysis will be conducted using Microsoft Excel 2016 and SPSS 25.0 statistical software (IBM Corporation, Armonk, NY, United States). An independent statistician, blinded to group assignment, will perform the statistical analysis. All data will be analyzed according to the intention-to-treat (ITT) protocol, regardless of adherence, provided participants receive at least one acupuncture treatment session and complete a baseline assessment of the primary outcome. Missing values will be imputed using the last observation carried forward method. The per-protocol (PP) population, comprising all randomized patients who completed more than 80% of the treatment procedure, will also be analyzed. All statistical tests will be two-sided, with a *p* value of <0.05 considered statistically significant. Categorical variables will be reported as medians (interquartile ranges), while continuous variables with normal distributions will be presented as means ± standard deviations. The chi-square test or Fisher’s exact test will be employed to compare dichotomous data from baseline demographic and clinical information. Measurement data include various scale scores and indicators of inflammatory cytokine expression levels. For normally distributed variables, an independent samples t-test will be used for between-group comparisons, and a paired samples t-test for within-group comparisons before and after therapy. Comparisons at multiple time points will be made using repeated-measures analysis of variance. The Mann–Whitney U test will be utilized for non-normally distributed variables in intergroup comparisons to analyze changes in efficacy outcomes. The comparison of multiple time points will be based on the generalized estimating equation (GEE). Multiple linear regression analysis will be employed to examine correlations between clinical efficacy and inflammatory cytokines.

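### The sample size treats dropouts as absent, but the ITT/LOCF analysis keeps them as non-responders, so the stated 90% power does not describe the planned primary analysis

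*Protocol article*

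**What the plan says.** **Sample size (section 2.6).** Earlier studies "reported a total effective rate of 13.72% for the 8-week MoCA score in the sham acupuncture group after treatment". For the other arm: "We anticipated a total effective rate of 58.33% for the 8-week MoCA score post-treatment in the verum acupuncture group". With two-sided alpha 0.05, the section claims "a power of 0.9, accounting for a 20% attrition rate, and an equal 1:1 group allocation, a minimum of 25 cases per group", 50 patients in total. It names the software, but not the test or variance option, and does not say whether the two rates refer to completers or to all patients treated.

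**Endpoint (section 2.7.1).** The primary outcome is binary: the share of all cases whose MoCA rises by at least 12% from baseline to week 8. A change from −12% to below 12% is classed as Invalid.

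**Timing (Table 1).** MoCA is scheduled at weeks 0, 8 and 14 only.

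**Analysis (section 4).** The ITT set is everyone with at least one session and a baseline primary-outcome assessment. "Missing values will be imputed using the last observation carried forward method". The chi-square or Fisher's exact test "will be employed to compare dichotomous data from baseline demographic and clinical information". No test is named for the effective rate.

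**The concern.** Dividing a sample size by (1 − attrition) is right when patients who leave contribute no outcome. Section 4 gives them one. With no MoCA between baseline and week 8, the only value to carry forward for a patient lost before week 8 is the baseline score. The improvement rate is then exactly 0%, the patient is Invalid, and the case stays in the denominator. Attrition therefore does not shrink the groups. It lowers the effective rate in both arms and narrows the difference that the test has to detect.

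The trial has 50 patients and one primary endpoint. If power for the planned analysis is below the stated 90%, the risk of missing the assumed effect is larger than readers are told, and a null result would be read with too much confidence.

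**Working it through.** **Inputs.** p1 = 0.1372, p2 = 0.5833, two-sided alpha 0.05, power 0.90, attrition 20%, 25 per arm (all section 2.6). The ITT set and LOCF rule are from section 4, the MoCA schedule from Table 1 and the response categories from section 2.7.1.

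**1. Reproducing 25 per arm.** Unpooled normal approximation:

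n = (z₀.₉₇₅ + z₀.₉₀)² × [p1(1−p1) + p2(1−p2)] / (p2−p1)²

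- (1.960 + 1.282)² = 10.507
- variance sum = 0.1184 + 0.2431 = 0.3614
- (0.4461)² = 0.1990
- n = 10.507 × 0.3614 / 0.1990 = 19.08, so 20
- 20 / 0.8 = 25, an exact match

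The other two-sided formulas tried, inflated the same way, do not give 25: arcsine 22 → 28, pooled 23 → 29, continuity-corrected 27 → 34. The stated 90% thus appears to belong to 20 completers per arm.

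**2. Power in 20 completers per arm** (exact binomial enumeration at 13.72% v 58.33%): unpooled Z 90.3%, Pearson 87.7%, Fisher 80.1%.

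**3. Power under the ITT/LOCF rule, 25 per arm.** Let q be the share lost before week 8 but after at least one session, equal in both arms, and take the planning rates as completer rates. The rates compared become p × (1 − q). At q = 0.20:

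- verum 0.5833 × 0.8 = 0.4666
- sham 0.1372 × 0.8 = 0.1098
- difference 35.7 points instead of 44.6

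Exact power with 25 per arm:

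| Lost before week 8 | Rates compared | Unpooled Z | Pearson | Fisher |
|---|---|---|---|---|
| 20% | 46.7% v 11.0% | 86.0% | 83.9% | 72.8% |
| 15% | 49.6% v 11.7% | 88.7% | 87.0% | 77.4% |
| 11.4% (20% spread evenly over 14 weeks: 20% × 8/14) | 51.7% v 12.2% | 90.4% | 88.9% | 80.5% |
| 10% | 52.5% v 12.3% | 91.0% | 89.7% | 81.7% |
| Rates already ITT (no dilution) | 58.3% v 13.7% | 94.7% | 94.1% | 89.0% |

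**4. What 90% would take in the first row.** 31 per arm (Pearson) or 36 per arm (Fisher). These are given for scale only, not as a proposal.

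**The case against.** **The sample size is arithmetically sound.** This stands. A reader might infer a miscalculation, but 25 follows exactly from a standard formula, and the unpooled Z test has 90.3% exact power in 20 per arm. The 20-then-25 route is a reconstruction, since section 2.6 does not state its formula. The point is a mismatch of basis between two sections, not an error of arithmetic.

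**Pearson and Fisher are not assigned to the primary endpoint.** This also stands. A reader might infer that the trial's own primary test has only 73% power. The document does not support that, because it names these tests only for baseline dichotomous data, and the choice for the effective rate may be made in an SAP that is not shown. The Fisher figure is the low end of a range. At 20% loss, however, even the test that reproduces the sample size falls to 86%, so the shortfall there does not depend on choosing Pearson or Fisher.

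**The 20% need not all fall before week 8.** Observation lasts 14 weeks, and losses after week 8 leave the primary endpoint untouched. Patients lost before a first session leave the ITT set altogether. With 10% to 11.4% lost before week 8, Pearson and unpooled Z are within about one point of 90%; Fisher stays near 80% to 82%. On the other side, attrition allowed for in sizing an 8-week endpoint is most naturally loss before week 8.

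**The planning rates may already be ITT rates.** The document does not say. If they are, power is about 90% or better (Fisher 89%), and the attrition allowance had no purpose. Either way, sections 2.6 and 4 rest on different bases.

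**Conclusion.** The mismatch is real: section 2.6 removes dropouts, while section 4 retains them and the MoCA schedule makes each pre-week-8 loss a non-responder. Its size is conditional. If the planning rates are completer rates and the full 20% is lost before week 8 but after at least one session, equally in both arms, the chance of missing the assumed effect is about 14% (unpooled Z), 16% (Pearson) or 27% (Fisher), against a stated 10%.

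A reader might conclude outright that 90% power is not delivered. The document does not support that without these conditions, none of which it states: milder timing brings Pearson or unpooled Z close to 90%, and ITT rates bring them above it. This is an inconsistent sample-size basis that should be corrected, but it does not invalidate the design and falls short of a must-fix.

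**What to change.** Keep 50 patients and leave the analysis rules as they are. In section 2.6:

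- name the test for the primary rate;
- say whether 58.33% and 13.72% are completer or ITT rates;
- restate the power for the ITT/LOCF analysis.

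If the rates are completer rates and Pearson's test is chosen, suitable wording would be: *With 25 per arm, power is about 84% (Pearson chi-square) if 20% are lost before week 8 and count as not improved; it is about 88% in 20 completers per arm.* If the rates are ITT rates, say so and drop the attrition adjustment from the justification.

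The cost is about one sentence and, on the completer reading, a less favourable stated power. No patients are added. Recruitment is still under way (20 enrolled according to section 5), so the correction can be made before the data are analysed.

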### Outcome measures

2.7

#### Primary indicator

2.7.1

The primary outcome measure is the total effective rate of the 8-week MoCA score. Changes in the MoCA score from baseline to the end of treatment and the follow-up period will assess patients’ cognitive function. The MoCA, a concise cognitive function assessment tool comprising 12 items, was developed by Nasreddine in 2005. It evaluates visuospatial abilities, executive function, short-term memory, language, and orientation to time and place (19). The MoCA test has a maximum score of 30 points, with scores between 21 and 26 indicating mild cognitive impairment. For individuals with 12 or fewer years of education, one point is added to the final score (37). The lower the score, the worse the cognitive function. To evaluate cognitive function, the MoCA score and total improvement rate will be assessed at baseline, at the conclusion of treatment, and during the follow-up period. The score of the MoCA, the absolute changes in scores from baseline to the end of treatment, and the follow-up period will be recorded. The minimum clinically significant difference of MoCA is 1.22 points (38). Improvement rate = [(posttreatment score − pretreatment score)/pretreatment score] × 100%. The curative effect is judged as follows: Significantly effective: Improvement rate≥20%; Effective: 12% ≤ Improvement rate<20%; Invalid: −12% ≤ Improvement rate<12%; Total effective rate according to the formula: (Significantly effective + Effective)/Total cases×100%.

